### Summary of the risk-benefit balance and risk-benefit balance between standard and study treatments

As both VA and TIVA are standard therapy, there is no significant risk-benefit imbalance between VA and TIVA. This study is a superiority test, but it is unclear which drug has superiority.

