### Rationale for setting up endpoints

The golden standard of the marker of liver damage ins transaminases(AST and ALT).^13)^ In many clinical studies, postoperative transaminases are used to evaluate liver damage. ^5)-11)^ As it was confirmed that the peak values of transaminases were within 3 days after surgery at preliminary retrospective study at our hospital, we set peak transaminases for 3 days after surgery as primary endpoint. As AST seems to be superior than ALT for assessment of liver damage at previous studies, we set AST as primary endpoint and ALT as important secondary endpoint. Referring to previous studies and preliminary study in our hospital(Sevoflurane 658±460 IU/L vs Propofol 351±178 IU/L), the judgement that the degree of liver damage differs depending on the anesthetics was a difference of AST as 300 IU/L..

As both IRI and oxidative stress affect systemically, postoperative adverse event is important outcome. However, as we set metastatic liver tumor resection as target of this study to assess the effect of anesthetics on liver damage, postoperative adverse event may be very low(rate of adverse event as JCOG grade 2 or more after metastatic liver resection is about 1% in our hospital). Thus, we set adverse event as secondary endpoint. And, as massive liver damage may induce prolonged liver dysfunction, postoperative peak total bilirubin is also important endpoint. However, as well as serious postoperative adverse event, the rate of prolonged liver dysfunction after metastatic liver tumor resection is very low. Thus we set peak total bilirubin as secondary endpoint.

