Upon receiving the report from the Principal Investigator, the Research Office will judge the urgency, importance, degree of impact, etc. of the report content, and if necessary, entrust the hospital director and the director to determine whether it is necessary to suspend registration or to notify the facility of information urgently.

- - 1. **Notifying Researchers in the Facility**

The Secretariat/Principal Investigator shall notify the Researcher in the Institute of the decision of the Secretariat/Principal Investigator in writing (e-mail is acceptable) regarding serious adverse events.

1. **Statistics**
   1. **Main analysis and criteria**

The main analysis is to compare the highest AST values within 3 days postoperatively in groups A and B by t-test, and judge a significant difference of less than 0.05 to be statistically significant. As a criterion for determining that the degree of IRI differs depending on the anesthetic, a difference of about AST 300 U / L was observed. This was based on the idea that a difference of about AST300U/L would have a significant impact on clinical anesthetic selection. If necessary, sensitivity analysis will include a population of patients who have completed protocol treatment (PPS), or a population of all randomized cases and supplemented with the worst values observed in groups A and B in cases where primary endpoint data are missing.

- 1. **Planned number of registrations, registration period, tracking period**

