Currently, the ischemic method that alleviates IRI is considered to be the intermittent ischemia method, and in consideration of the effect of IRI on the whole body, the intermittent ischemia method is also adopted in our hospital. However, previous studies used continuous ischemia, which strongly expresses IRI, except for one group in the 2012 Beck-Schimner et al. trial, and the mean, median, standard deviation, and quartile values of postoperative AST values are likely to differ from the results of this postoperative ischemia. Therefore, we mainly referred to the results after intermittent ischemia and the results of our retrospective studies in the previous study, and the other studies were only secondary references. First, postoperative AST was treated as normally distributed. Next, clinically, it was judged that a difference of about 300 U/L of AST had a significant impact on anesthetic drug decision. The standard deviation of AST is expected to be 300 U/L. Finally, the significance difference was set to 0.05 and the detection power was set to 0.8. Under these conditions, 28 patients in each group (56 patients in total) were calculated to be required. The number of such surgical cases is about 40 per year at our single facility, and about 70% of them are liver tumor resection in less than 5 places and the liver is completely removed less than 5 areas of Couinaud. The annual enrollment rate for this trial is estimated to be around 17, with an expected participation consent acquisition rate of 60%, and the planned registration period is expected to be 3 years and 3 months. The follow-up period shall be 28 days postoperatively, which is the definition of postoperative complications.

- 1. **Interim analysis and early discontinuation of the study**

　　　　　No early discontinuation of interim analyses or trials is planned.

- 1. **Analysis in secondary endpoints**

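### The stated inputs (difference 300 U/L, SD 300 U/L, alpha 0.05, power 0.8) give 17 patients per group, not 28, so at least one planning figure is wrong

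*Protocol*

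**What the plan says.** The calculation is in the Protocol, Statistics section, under the planned number of registrations. It proceeds in order:

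- Distribution: "First, postoperative AST was treated as normally distributed".
- Difference: "it was judged that a difference of about 300 U/L of AST had a significant impact on anesthetic drug decision".
- Variability: "The standard deviation of AST is expected to be 300 U/L".
- Error rates: "the significance difference was set to 0.05 and the detection power was set to 0.8".
- Result: "Under these conditions, 28 patients in each group (56 patients in total) were calculated to be required".

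The test to be powered is given in the same section: "The main analysis is to compare the highest AST values within 3 days postoperatively in groups A and B by t-test". The section on risk-benefit balance names no favoured direction: "This study is a superiority test, but it is unclear which drug has superiority". The synopsis repeats the total of 56. The rationale for the endpoints reports the hospital's own preliminary peak AST as "Sevoflurane 658±460 IU/L vs Propofol 351±178 IU/L", and the sample-size paragraph says that in-house retrospective results and results after intermittent ischaemia were its main references. No interim analysis is planned.

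**The concern.** The paragraph presents 28 as the direct result of the inputs listed just before it. A difference equal to one SD is a large standardised effect, and 28 per group is far more than such an effect needs at 80% power.

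This paragraph is the only justification for 56 patients. The registration period of 3 years 3 months rests on it too: 56 patients at about 17 per year is 56/17 = 3.3 years. If the inputs are right, 34 patients would have met the stated target, and 56 − 34 = 22 more are randomised than the calculation requires. If the number is right, an input is misreported, and the stated power belongs to some other set of assumptions. Either way, a reader cannot tell what difference the trial was designed to detect, or with what power. That matters because 300 U/L is the protocol's own threshold for a difference that would affect the choice of anaesthetic.

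**Working it through.** **Inputs.** Difference Δ = 300, SD σ = 300, alpha 0.05, power 0.80, 1:1 allocation, two-sample t-test, no inflation (all from the Statistics section). Sidedness is not stated. Two-sided is assumed because no direction is specified; one-sided is also tried.

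**Step 1. Try to reproduce 28 (normal approximation).**

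n per group = 2(z₀.₉₇₅ + z₀.₈₀)² (σ/Δ)² = 2(1.960 + 0.842)² × (300/300)² = 2 × 7.849 × 1 = 15.7, so 16.

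**Step 2. The planned t-test (noncentral t, df = 2n − 2, noncentrality Δ/(σ√(2/n))).**

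| n per group | Power |
|---|---|
| 16 | 0.781 |
| 17 | 0.807 |
| 28 | 0.957 |

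The requirement is 17 per group, 34 in total. The stated 28 is 28/17 = 1.65 times that. One-sided testing moves further away: 13 by normal approximation, 14 by t-test.

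**Step 3. Look for a bridge from 17 to 28.**

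- Dropout: it would take a loss of 1 − 17/28 = 39%. None is stated, and the endpoint uses routine blood tests on the first three postoperative days.
- Interim looks: none planned.
- Rank-test efficiency: 17/0.955 = 17.8 and 17/0.864 = 19.7, so at most 20.
- Preliminary data: the root-mean-square SD is √((460² + 178²)/2) = √121,642 = 348.8. With Δ = 300, the normal approximation gives 15.7 × (348.8/300)² = 21.2, so 22; the t-test gives 23. With the observed difference of 658 − 351 = 307, the t-test gives 22.

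None reaches 28.

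**Step 4. Which changed input would give about 28?**

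| Input changed, others as stated | Normal approximation | t-test |
|---|---|---|
| SD 400 | 15.7 × (400/300)² = 27.9, so 28 | 29 |
| SD 387 to 393 | 27 to 28 | 28 |
| Difference 229 to 233 | 27 to 28 | 28 |
| Power 0.95 | 26 | 27 |

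These are back-solved. The protocol gives none of them as a planning value.

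**Step 5. What 28 per group delivers (two-sided t-test, alpha 0.05).**

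| SD | Power for 300 U/L | Difference detectable at 80% power |
|---|---|---|
| 300 (stated) | 0.957 | 229 U/L |
| 349 (preliminary data) | 0.885 | 266 U/L |
| 390 | 0.807 | just under 300 U/L |
| 400 | 0.787 | 305 U/L |

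Power for 300 U/L reaches 0.80 at an SD of about 393 and is lower beyond that.

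**The case against.** The best case for leaving the paragraph alone is that the discrepancy runs in the safe direction. At the stated SD the trial has more power than claimed, and at the SD implied by the preliminary data it still has 0.885. The endpoint, test and significance level are untouched, and the protocol regards both anaesthetics as standard treatment, so the extra patients face no added experimental treatment. All of that stands, and it limits the consequence. It does not make the statement correct: the paragraph ties 28 to its listed conditions, and those conditions give 17.

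The wording that the difference is only about 300 U/L does not help. At SD 300, 28 per group corresponds to about 229 U/L. Nor is this a detail left to a statistical analysis plan, because the protocol states both the inputs and the result.

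A mismatch with the preliminary data is not a second error. The paragraph says it also drew on intermittent-ischaemia results, so its SD need not equal 349. It does mean that the source of 300 should be named.

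A reader might infer that the planners really used an SD of 400. The documents do not support this: 400 gives 28 only by normal approximation, the planned t-test then needs 29, and a smaller difference or a power of 0.95 comes about as close.

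**Conclusion.** The stated sample size does not follow from its stated inputs: 28 per group against 17 (16 by normal approximation), a 65% excess. At least one planning figure is wrong or a step is undisclosed, and the protocol does not show which. This rests on a two-sided t-test with equal groups and a common SD; a one-sided test widens the gap.

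Two stronger readings are not supported. A reader might infer that the trial is underpowered. It is not shown to be: power for 300 U/L stays at or above 0.80 for any SD up to about 393, and even at 400 the shortfall is about one percentage point. A reader might also infer that a null result could not be interpreted. It could be, from the estimated difference and its confidence interval, whatever SD was written down at planning. What is lost is a reproducible justification and a true statement of the design's power.

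**What to change.** Keep 56 patients. Cutting to 34 would be safe only if the SD really is 300; at the preliminary-data SD of 349, 17 per group would have power of only 0.68 for 300 U/L (same t-test formula with n = 17).

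The sponsor should identify the inputs actually used and the source of the SD, then restate the paragraph as one consistent set, including the sidedness and any allowance for missing data:

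- If SD 300 stands, state power as about 0.96 for 300 U/L or, equivalently, 80% for 229 U/L, and say that 56 exceeds the 34 needed for 80% power.
- If another SD was used, state it and the power it gives: 0.885 at 349, for example, or 0.807 at 390 and 0.787 at 400. Values near 390 to 400 are only a back-solved possibility and should not be adopted unless the planning records show them.
- If a different difference or power was used, state that instead.

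The cost is one paragraph of protocol wording and the ethics committee approval that the protocol requires for revisions. Enrolment, treatment and analysis do not change.

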# Evaluation items, clinical tests, and evaluation schedule

- 1. **Items to be collected before registration (using information from the anesthesiology preoperative outpatient clinic)**

Patient background (age, sex, primary cancer type, preoperative complications [Charlson Index], presence or absence of preoperative chemotherapy [drug used if performed], allergic history), ASA-PS, biochemical tests (AST, ALT, Bil)

- 1. **Observation period**

The observation period will be up to 28 days after surgery to assess postoperative complications in both groups. If protocol treatment is discontinued in any group, no observation period is set.

- 1. **Items to be collected during the treatment period**

Surgical method, anesthesia method, operative time, anesthesia time, number and total weight of resected liver, total ischemic time, intraoperative blood loss, intraoperative fluid/transfusion volume, intraoperative urine volume.

- 1. **Evaluation items after the end of treatment**
     1. **Primary outcome**
- Liver damage:

Assessed with the highest value of AST 3 days postoperatively.

In addition, the results of postoperative biochemical tests (tested daily for 3 days after surgery) that are usually performed in clinical practice will be used, and blood collection and testing for this study will not be performed.

- - 1. **Secondary outcome**
- Liver damage

As a particularly important secondary endpoint, the highest ALT value at 3 days postoperatively will be evaluated. In addition, the results of postoperative biochemical tests (tested daily for 3 days after surgery) that are usually performed in clinical practice will be used, and blood collection and testing for this study will not be performed.

- Early postoperative liver function evaluation

Assessed at the highest value of Bilirubin 3 days postoperatively. In addition, the results of postoperative biochemical tests (tested daily for 3 days after surgery) that are usually performed in clinical practice will be used, and blood collection and testing for this study will not be performed.

- Postoperative adverse event

JCOG postoperative complication criteria (Clavien-Dindo classification) Collect postoperative complications of grade II or higher for 28 days postoperatively.

- 1. **Evaluation Schedule**

|  | pretreatment | postoperative | | | |
| --- | --- | --- | --- | --- | --- |
|  | Anesthesiology outpatient | Day 1 | Day 2 | Day 3 | 〜 28 days |
| Characteristics | ○ | - | - | - | - |

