| ASA-PS | ○ | - | - | - | - |
| AST | ○ | ○ | ○ | ○ | - |
| ALT | ○ | ○ | ○ | ○ | - |
| Bilirubin | ○ | ○ | ○ | ○ | - |
| Postoperative advese event | - | ○ | ○ | ○ | ○ |

1. **Effect Determination and Endpoint Definition**

Including animal experiments, transaminase values are used as an evaluation item for ischemia-reperfusion injury in the liver region.^13)^ In clinical studies on ischemic reperfusion disorder after liver resection, the highest transaminase values in the early postoperative period have been used. ^5)-11)^ Since the purpose of this study is to evaluate ischemic reperfusion damage in the liver region, it will be adopted as a primary endpoint. Based on previous studies including retrospective studies (especially those by Beck-Schimner et al.), AST was considered to be more useful than ALT, and AST was selected as the primary endpoint in this study, and ALT was analyzed as an important secondary endpoint. There is no difference in the effect on postoperative AST and ALT between 15 and 30 minutes for one blood flow blockade.^16)^。

IRI is a condition that can adversely affect the whole body, and serious postoperative complications are considered to be important endpoints. However, since this study included metastatic liver tumor resection to assess the effect of anesthetics on IRI, the incidence of serious postoperative complications is expected to be very low (the incidence of serious complications after metastatic liver tumor resection in our hospital in the last two years is 1%). Therefore, it was set as a secondary endpoint. In addition, Bil, which is also an important endpoint, because severe ischemia-reperfusion injury disorder can cause liver damage from the early postoperative stage. However, as with serious postoperative complications, early postoperative liver damage is very unlikely, so it was set as a secondary endpoint.

- 1. **Define the target population**

Following the intent-to-treat principle, the analysis will be a population consisting of all randomized cases excluding cases with no data on the randomized primary endpoint (Maximum Analysis Set (FAS)).In addition, when discontinuation of protocol treatment occurs, analysis will be performed in a population of patients who have completed protocol treatment (Per Protocol Set: PPS).

- 1. **Defining Endpoints**
- Primary endpoint

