The maximum AST value within 3 days after surgery. In a retrospective study of metastatic liver tumor resection in the last 2 years, it was confirmed that the highest value in the early postoperative period was achieved within 3 days after surgery, so it was set as the highest value within 3 days after surgery.

- Secondary endpoint

Set the highest ALT value within 3 days postoperatively as an important secondary endpoint. As other endpoints, the JCOG postoperative complication criterion (Clavien-Dindo classification) Grade II or higher postoperative complications and the highest Bil-value within 3 days after surgery as a liver function evaluation are used.

1. **Reporting Adverse Events and Defects**

In the event of a "serious adverse event" or "unexpected adverse event", the attending physician should report it to the Research Secretariat/Principal Investigator. The events listed in the package insert are not counted as adverse events in this study.

Report to the Minister of Health, Labour and Welfare on adverse reactions based on the Act on Securing Quality, Efficacy and Safety of Pharmaceuticals and Medical Devices (Address: Safety Information Division, Safety Department 1, Pharmaceuticals and Medical Devices Agency, [contact], Email: [[contact])](mailto:[contact])17)「,)^[17)](mailto:[contact])17)「,)^[,](mailto:[contact])17)「,) Based on the "Ethical Guidelines for Medical Research Involving Human Subjects" (Ministry of Education, Culture, Sports, Science and Technology / Ministry of Health, Labor and Welfare Notification No. 18), the director of the medical institution reports unexpected serious adverse events to the Minister of Health, Labour and Welfare, etc., and the medical institution to the company to communicate side effects to the company, it is the responsibility of the principal investigator to appropriately report to the head of the medical institution at each facility.

- 1. **Emergency Reportable Adverse Events**

Adverse events that fall under any of the following are designated as "serious".

1. Any death during protocol treatment, regardless of whether or not there is a causal relationship with protocol treatment.
2. Death after completion of protocol treatment and a causal relationship with the protocol cannot be ruled out. Obvious death from primary disease does not apply.
3. Life-threatening:

Grade 4 non-hematologic toxicity or equivalent in CTCAE v4.0.

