As an important secondary endpoint, the highest ALT value within 3 days postoperatively for ischemia-reperfusion injury was compared in two groups by t-test, and a significant difference of less than 0.05 was statistically significant. For postoperative complications within 28 days, the Fisher test compares the two groups, with a significant difference of less than 0.05 as statistically significant. Regarding liver function, the highest bilirubin value within 3 days after surgery was compared in two groups by t-test, and a significant difference of less than 0.05 was considered statistically significant.

- 1. **Final Analysis**

In addition to the analyses described in 10.1 and 10.4, multivariate logistic analyses are performed to exclude the effects of non-anesthesia methods on IRI.

- 1. **End of research**

The research will end with the publication of all papers related to this study.

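### The supplementary adjusted analysis of ischaemia-reperfusion injury is specified as logistic regression, although the protocol measures that injury only by continuous peak AST and ALT

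*Protocol*

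**What the plan says.** The section Effect Determination and Endpoint Definition ties transaminases to IRI: "Since the purpose of this study is to evaluate ischemic reperfusion damage in the liver region, it will be adopted as a primary endpoint". Defining Endpoints makes the primary endpoint a continuous laboratory value: "The maximum AST value within 3 days after surgery".

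Main analysis and criteria sets the primary test: "The main analysis is to compare the highest AST values within 3 days postoperatively in groups A and B by t-test". Analysis in secondary endpoints treats ALT in the same way: "the highest ALT value within 3 days postoperatively for ischemia-reperfusion injury was compared in two groups by t-test".

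Final Analysis then adds, on top of those analyses, that "multivariate logistic analyses are performed to exclude the effects of non-anesthesia methods on IRI". It names no outcome variable, threshold or covariates. The 300 U/L figure in the main-analysis and sample-size sections is a difference between groups, not a value that classifies a patient as having or not having IRI.

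**The concern.** Logistic regression needs a categorical outcome, and the protocol has none for IRI. To run the stated model, someone must dichotomise peak AST or ALT. That has three consequences.

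- The adjusted result becomes an odds ratio for exceeding a threshold. It cannot be set beside the t-test's difference in U/L or judged against the 300 U/L criterion.
- Information within each category is discarded, so the adjusted analysis is weaker than it need be.
- The result depends on which threshold is used.

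The protocol's background section says that many factors affect transaminases, naming resected size and ischaemic time among them, and randomisation uses no adjustment factor. In 56 patients, this regression is the planned analysis that addresses chance imbalance in such factors. It should estimate the same quantity as the main test, with comparable precision.

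**Working it through.** **Inputs.** From the sample-size section: difference 300 U/L, SD 300 U/L, significance level 0.05, power 0.80, 28 per arm, and "postoperative AST was treated as normally distributed". Two-sided testing is assumed, because the protocol says it is unclear which drug is superior. From Rationale for setting up endpoints: preliminary means ± SD of 658 ± 460 (sevoflurane) and 351 ± 178 (propofol).

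**Step 1: the plan's own figure.** n per arm = 2 × [(1.960 + 0.842) × SD / difference]² = 2 × (2.802 × 300/300)² = 15.7, so 16 (17 with the exact t-test). The stated 28 does not follow from SD 300. With SD 400 the formula gives 2 × (2.802 × 400/300)² = 27.9, so 28. That discrepancy is a separate matter. It matters here only because the power comparison has to be shown at both SDs.

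**Step 2: continuous analysis, 28 per arm.** t-test power is about 96% at SD 300 and about 79% at SD 400.

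**Step 3: dichotomise midway between the group means.** The proportion above the cut is Φ(+difference/2SD) in one group and Φ(−difference/2SD) in the other. Power = Φ[(d − 1.96 × SE0)/SE1], with SE0 the pooled and SE1 the unpooled standard error of the difference d in proportions.

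- SD 300: Φ(±0.5) gives 69.1% and 30.9%, so d = 0.383. SE0 = √(2 × 0.25/28) = 0.134 and SE1 = √(2 × 0.309 × 0.691/28) = 0.123. Power = Φ(0.98) = 84%.
- SD 400: Φ(±0.375) gives 64.6% and 35.4%, so d = 0.292. SE0 = 0.134 and SE1 = 0.128. Power = Φ(0.24) = 59%.

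Patients needed per arm for 80% power at this cut are 26 instead of 16 (SD 300) and 45 instead of 28 (SD 400), about 60% more in each case.

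**Step 4: simulation of a median split against the t-test** (20,000 trials, 28 per arm).

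| Model for peak AST | t-test | Median split |
| --- | --- | --- |
| Normal, difference 300, SD 300 | 96% | 86% |
| Normal, difference 300, SD 400 | 79% | 64% |
| Lognormal, preliminary means and SDs | 96% | 85% |
| Gamma, preliminary means and SDs | 94% | 73% |

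Simulating the midpoint cut of step 3 gives about 83% (SD 300) and 58% (SD 400). With the median split, this yields the ranges 83-86% and 58-64%.

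**Step 5: dependence on the cut.** By the step 3 formula, a cut 1 SD from the midpoint gives 65% (SD 300) or 43% (SD 400). Under the gamma model, likelihood-ratio power runs from 14% (cut at 200 U/L) through 69% (400) to 91% (600).

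**Step 6: with covariates.** Three covariates explaining 30% of the variance (an assumption; the protocol gives no such figure) and a midpoint cut give linear against logistic power of 98% against 89-90% at SD 300, and 88% against 68-71% at SD 400. With a cut 1 SD above the midpoint, 9-16% of logistic fits failed to converge or separated.

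**The case against.** The strongest reply is that this analysis is supplementary. The conclusion rests on the t-test, the sample size was set for the t-test, and randomisation makes the unadjusted comparison valid. All of that stands. A reader might infer that the trial as a whole loses power; the protocol does not support that, because the loss is confined to the adjusted analysis.

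Second, the threshold and covariate list are details that a statistical analysis plan may supply before any outcome is seen. That also stands. A reader might infer that the cut will be picked with the data in hand, but nothing in the protocol says so, and the absence of a cut-point is not itself the fault. What a later plan cannot do is remove the mismatch: it must either dichotomise AST or contradict the protocol's stated model.

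Third, a reader might suppose that the logistic model is meant for the binary endpoint, complications, and object that events are too few. The text directs the model at IRI and gives complications Fisher's test, so no multivariable complications model is planned and that argument falls away.

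Fourth, a reader might infer that the model will adjust for intraoperative variables. The protocol names no covariates, and pre-registration factors are collected too. This is a point to settle in the rewording, not an error already made.

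Finally, the size of the loss depends on assumptions. On the protocol's own SD of 300, a central or median cut still leaves power above the 80% target, and under the gamma model a favourable cut (600 U/L) comes close to the t-test. The larger losses need SD 400, skewed data or an off-centre cut.

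**Conclusion.** The point holds as a mismatch between model and endpoint in one supplementary analysis. IRI is continuous wherever the protocol defines or tests it, and the adjusted analysis is nevertheless fixed as logistic. At 28 per arm and a difference of 300 U/L, the cost to that analysis is about 10 to 13 percentage points at SD 300 (96% to 83-86%) and about 15 to 21 at SD 400 (79% to 58-64%), for a median or central cut. These figures assume two-sided 5% testing and normally distributed AST. SD 400 is not a protocol figure; it is the value at which 28 per arm gives about 80% power. The change of estimand, from a difference in U/L to an odds ratio, does not depend on any of these assumptions. It should be corrected, but the primary test and its interpretation are untouched.

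**What to change.** In Final Analysis, replace the logistic model with multiple linear regression (ANCOVA) of peak AST, and likewise of peak ALT. Report the adjusted treatment difference in U/L with its confidence interval, so that it can be read against the 300 U/L criterion.

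- **Scale.** Keep the original scale for this analysis and use a log-scale version only as a sensitivity analysis. A log-scale model leaves the absolute criterion, and under the gamma model a log-scale t-test has only about 76% power against 94% on the original scale.
- **Covariates.** Use treatment plus a few covariates fixed before randomisation and already in the pre-registration list, for example baseline AST or ALT and preoperative chemotherapy.
- **Intraoperative variables.** The treatment-period items include "number and total weight of resected liver, total ischemic time, intraoperative blood loss". Ischaemic time and resected weight are measured after randomisation, so place them only in a separately labelled supportive model.
- **Binary version, if wanted.** State the threshold in advance and label the analysis supportive.

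The cost is a protocol wording change with ethics committee approval, ideally before outcomes are examined by group. No new data are needed for the covariates named here.
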